### Participant Reimbursement

Consistent with the Australian guidelines for acknowledging the time and value of consumer participation [75], participants will be offered modest reimbursement for any time, travel, and inconvenience associated with participation in the study assessments (supermarket voucher to the value of AUD $19.60 for baseline and 2-month follow-up assessments; AUD $1=US $0.65).

### Statistical Analysis

#### Primary Objectives

Given the primary objectives of exploring feasibility and acceptability, outcome data will primarily utilize descriptive statistics (eg, summarizing the recruitment rate, proportion of missing data, data analytics, MARS and uMARS quality ratings, and D-WAI alliance ratings). Descriptive statistics will be supplemented by the following cost and qualitative analyses.

##### Cost Analysis

A cost analysis will be conducted with the assistance of the health economics unit at the Hunter Medical Research Institute, Australia. The analysis will adopt a health provider perspective; it will measure and report the cost associated with developing and maintaining Smart Track. This is policy-relevant information as it estimates the resources required to translate the model of care to another location. Cost modeling will be conducted to report the direct costs of the additional resources required to develop and maintain Smart Track. The perspective adopted will be limited in the base case analysis to that of the health provider. Costs and resource use will be prospectively collected for the duration of the feasibility study and will be valued using a combination of hospital data from NSW Health, Medicare Benefits Schedule tariffs, and market rates. Downstream cost savings associated with hospitalization will also be explored.

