### This Study

In this paper, we detail the study protocol for a nonrandomized, prospective, single-arm pilot study, with a concurrent cost evaluation and nested qualitative evaluation designed to explore the feasibility and acceptability of a novel mHealth ROM and feedback app (*Smart Track*) in SMART Recovery groups coordinated by SRAU. The secondary objectives are to describe Smart Track usage patterns, psychometric properties of the ROM items, and participant-reported outcomes.

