### Participants

#### Eligibility

Participants must be at least 18 years of age, currently participating in one or more SMART Recovery groups located within New South Wales (NSW), have a current email address or be willing to obtain an email address, and be able to comprehend English at a level sufficient to complete study requirements.

Participants will be eligible irrespective of their self-reported computer and/or smartphone literacy. No restrictions will be placed on concomitant care, including the frequency or duration of SMART Recovery group participation or participation in other forms of AOD treatment. Participants will only be excluded if they are unable or unwilling to provide informed consent. Exclusion criteria were kept to a minimum to ensure that the study sample is representative of people attending SMART Recovery groups.

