##### Cost Analysis

###### Health Services and Medication: Usage and Cost

An adapted version of the Client Service Receipt Inventory (CSRI)—*generic* UK mental health [59] will be used to assess health services and medication usage. The content of this inventory has been updated to reflect key sources of mental health expenditure in Australia [60]. These data will allow us to explore clinical and treatment characteristics that may be associated with app usage and will provide some insight into costing.

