###### Time and Resource Utilization

Time and resource utilization will be captured in Microsoft Excel using a *cost capture template* [61-63]. This template will be used by the research team to maintain a record of cost data associated with the conduct of the study and the development and implementation of Smart Track. Only costs required to develop and implement the Smart Track app will be included in the cost analysis.

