### Study Outcomes

Primary and secondary endpoints are presented in Tables 3 and 4, respectively.

**Table 3 table3:** Primary endpoints.

Primary objective	Primary endpoint
To explore the feasibility of using Smart Track as part of SMART^a^ Recovery groups for the purposes of ROM^b^ and tailored feedback	Proportion of eligible participants who consent to the study Proportion of missing data for each of the ROM items/instruments at each week of administration, across the 2-month period of Smart Track usage Costs associated with developing Smart Track and maintaining the app until the completion of data collection Participant engagement with Smart Track, as indexed by data analytics captured daily across the data collection period
To explore the acceptability of using Smart Track as part of SMART Recovery groups for the purposes of ROM and tailored feedback	Detailed qualitative feedback from SMART Recovery group members and facilitators to explore their experience of and satisfaction with Smart Track (2-month follow-up) Quality ratings as assessed by participant and facilitator ratings of the user version of the Mobile App Rating Scale (2-week follow-up) and Mobile App Rating Scale (2-month follow-up), respectively Digital therapeutic alliance ratings as assessed by participant ratings of the Digital Working Alliance Inventory (2-week and 2-month follow-up)

^a^SMART: Self-Management and Recovery Training.

^b^ROM: routine outcome monitoring.

**Table 4 table4:** Secondary endpoints.

Secondary objective	Secondary endpoints
To explore how participants engage with the app and describe usage patterns	Demographic, clinical, and treatment factors (as measured by Client Service Receipt Inventory, COMS^a^, and SURE^b^ at baseline and 2-month follow-up) associated with (in)completion of Smart Track ROM^c^ items Data analytics captured daily across the data collection period
To provide preliminary evidence for the psychometric properties of the ROM items administered by Smart Track	Internal reliability and convergent and divergent validity of COMS and SURE items administered by Smart Track (relative to the complete versions administered at baseline and 2-month follow-up)

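### The cost analysis proposes to explore hospitalization savings, but this single-arm, 2-month study has no comparison from which a saving due to Smart Track could be estimated

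*Protocol article*

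**What the plan says.** The Cost Analysis text under Statistical Analysis takes a health provider perspective and states its output: "it will measure and report the cost associated with developing and maintaining Smart Track". It closes by adding: "Downstream cost savings associated with hospitalization will also be explored". The first primary objective in Table 3 (Study Outcomes) lists the matching endpoint, "Costs associated with developing Smart Track and maintaining the app until the completion of data collection". Neither Table 3 nor Table 4 contains a hospitalization or savings endpoint.

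Two other sections bear on costing. Under Health Services and Medication, an adapted Client Service Receipt Inventory "will be used to assess health services and medication usage", and its data are expected to inform costing to some degree. Table 2 schedules this inventory at baseline and 2-month follow-up only. Under Time and Resource Utilization, after describing the cost-capture template, the article says: "Only costs required to develop and implement the Smart Track app will be included in the cost analysis".

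The section This Study describes the design as a "nonrandomized, prospective, single-arm pilot study, with a concurrent cost evaluation". The Eligibility section requires current participation in a SMART Recovery group and adds: "No restrictions will be placed on concomitant care".

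**The concern.** A cost saving is a causal quantity: the hospital cost incurred with the app, set against the cost that the same people would have incurred without it. The design supplies the first term and nothing for the second. A fall in hospital use between baseline and 2 months could arise with no app effect at all. If it were valued in dollars and placed beside the cost of building and maintaining Smart Track, readers could take it as a return on the investment. The article's Conclusions name service providers and policy makers among the app's possible users, so such a reading could carry weight.

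**Working it through.** The plan states no figure for savings, so there is none to reproduce. The main check sets the stated aim against the data that the study will hold.

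**1. What a saving would need, and what is available**

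- *Concurrent comparator:* none; the study has a single arm (This Study).
- *Historical control, external effect estimate or decision model for savings:* none named. The only modelling in the Cost Analysis text concerns the direct costs of developing and maintaining the app. The NSW Health hospital data mentioned there are for valuing resources, not for comparison.
- *Comparison of heavier with lighter users:* use is self-chosen (Overview of the app), so the two groups would differ for reasons other than the app.
- *Participant-level hospital use:* the Client Service Receipt Inventory, at two time points 2 months apart (Table 2). Effects that appear later than 2 months, which the word downstream suggests, are not observed.

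What remains is the change in reported hospital use from baseline to 2 months.

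**2. What that change contains**

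- Any app effect.
- The effect of the SMART Recovery groups, which every participant already attends.
- The effect of other treatment, which is unrestricted.
- Time trend and regression to the mean. The Study Setting section says that groups are also held in inpatient services, so some people could be recruited around an admission. Whether any study site is of this kind is not stated.

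One arm cannot separate these parts.

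**3. Regression to the mean alone (assumed inputs)**

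Suppose the long-run mean and SD of hospital use are constant, the baseline mean lies 0.5 SD above the long-run mean, and the correlation between windows is ρ. With no app effect the expected fall is 0.5 × (1 − ρ) SD:

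- ρ = 0.3: 0.35 SD
- ρ = 0.5: 0.25 SD
- ρ = 0.7: 0.15 SD

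The 0.5 SD and the values of ρ are assumptions. The documents do not show that participants enter at a high point.

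**4. Sampling error (assumed inputs)**

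Let p be the proportion of participants with at least one admission per window, equal in both windows. The 95% half-width for the paired change is 1.96 × √[2p(1 − p)(1 − ρ)/n]. The target n = 100 is from the Power section; p and ρ are assumed.

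| p | ρ = 0 | ρ = 0.5 |
|---|---|---|
| 0.05 | 6.0 points | 4.3 points |
| 0.10 | 8.3 points | 5.9 points |
| 0.20 | 11.1 points | 7.8 points |

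For example, p = 0.10 and ρ = 0 gives 1.96 × √(0.18/100) = 0.083. Relative to p, the half-widths run from 39% (7.84/20) to 121% (6.04/5). If only 80 people were followed up (also an assumption), the range would be 4.8 to 12.4 points.

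Steps 3 and 4 are separate problems. A larger sample would shrink the half-widths in step 4 and leave the bias in step 3 unchanged.

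**The case against.** The strongest reply is that the article promises very little. Savings will only be explored; no test, net cost or cost-effectiveness ratio is planned, and no endpoint depends on them. The article condenses a fuller protocol, which may set out a scenario or threshold model prepared with the health economics unit. This holds as far as severity goes, and it means that a before-after comparison is an inference from the data schedule, not a stated method. It does not rescue the sentence. Exploring a saving still needs a counterfactual, and the article names none. A model fed by outside effect estimates would draw its saving from those estimates and not from this study. The Conclusions themselves leave effectiveness to future intervention studies.

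Two stronger readings are tempting, and the documents do not support them.

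- A reader might infer that the Time and Resource Utilization section flatly forbids a savings analysis. Its sentence follows the description of a template that also records the cost of conducting the study, and its most natural purpose is to keep those research costs out. It speaks of costs, not savings, and the section on health services and medication expects service-use data to inform costing. The sections need aligning, but this is not a firm contradiction.
- A reader might infer that savings share the standing of a primary endpoint, or that the article calls them policy-relevant. Both the endpoint and that description belong to the cost of developing and maintaining the app.

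**Conclusion.** The point holds in a limited form. The article sets out to explore a saving that its design cannot estimate: there is no comparator, concurrent care is unrestricted, follow-up is 2 months, service use is measured at two time points, and no outside counterfactual is named. This conclusion rests on the text alone and needs no assumed figure.

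The numerical size is not known. The half-widths of about 4.3 to 11.1 points and the regression-to-the-mean falls of 0.15 to 0.35 SD depend wholly on assumed admission rates, correlations and baseline elevation. They illustrate and do not predict. The documents also do not establish that a spurious saving would appear, or in which direction hospital use would move.

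Severity is minor, since the item is exploratory and outside Tables 3 and 4. The sentence is nevertheless wrong as written and should be changed.

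**What to change.** Replace the last sentence of the Cost Analysis text under Statistical Analysis with wording such as: *Hospital use reported on the Client Service Receipt Inventory, and its cost, will be described at baseline and at 2 months, over look-back windows of equal length and with 95% confidence intervals, as inputs for a later controlled evaluation. No saving will be attributed to Smart Track.*

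Keep the cost of developing and maintaining the app as the primary cost endpoint. Align the Time and Resource Utilization sentence with Table 3, the Cost Analysis text and the section on health services and medication, so that it covers maintenance, makes clear that study-conduct costs are what it excludes, and leaves room for the descriptive service-use data. Restricting the analysis to that sentence's literal scope would be a mistake, because it would drop the maintenance costs that the endpoint requires.

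The change costs a few lines of text. The inventory is already scheduled at both time points; its look-back windows need checking for equal length, since the article does not state them. The study gives up a savings statement that its design cannot support, and loses no data.

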##### Qualitative Evaluation

Qualitative data will be examined to inform the acceptability of Smart Track by exploring the participants’ and facilitators’ experiences of the perceived usefulness of ROM and any reason(s) for nonadherence. The analysis will proceed in 2 ways. First, we will identify key concepts and experiences to inform future development and/or refinement of Smart Track content, features, and/or procedures. Second, if there is sufficient data, an inductive approach [76] will be used to shed light on the ways in which individuals understand themselves and their actions (such as in the SMART Recovery group). The methodology also allows for individual beliefs and experiences to be positioned within broader social, service, and policy contexts, including factors such as drug treatment policy and service availability and social attitudes toward drugs and people who use them [77].

#### Secondary Objectives

##### App Engagement and Usage Patterns

A detailed exploration of the relationship between app usage (as indexed by frequency of ROM completion, number of missing items, and time to disengagement) and participant characteristics (demographic, clinical, and treatment variables) will be explored using linear regression. Furthermore, we intend to explore the ROM data graphically to see (1) whether it is likely to characterize particular patterns of usage and (2) whether these patterns appear to be influenced by various participant characteristics. Potential patterns that emerge during this exploratory phase will be followed up using latent trajectory analysis. This will clarify whether app use increases, decreases, or has some other pattern over time. Descriptive statistics will also be used to summarize app-generated data analytics.

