### Overview of the mHealth Routine Outcome Monitoring and Feedback App (Smart Track)

The Smart Track app was designed for participants attending SMART Recovery groups. ROM items are intended for weekly completion. However, it is up to the individual to decide whether, when, and how they engage with Smart Track. Given the low-risk, low-burden nature of this study, there are no contingencies for discontinuing access to the Smart Track app. Owing to app store regulations, Smart Track will not be restricted to study participants. It will be freely available for download through Android and iPhone Operating System stores (only data from those who provide consent will be included in the study).

Publications detailing the methods and findings from the qualitative work [33] and app development process (including theoretical foundations) will be reported separately. To provide context, a brief summary is presented here. The Smart Track app was developed during the first phase of this study using participatory design workshops and an iterative development process informed by the (1) consideration of existing ROM tools, (2) qualitative feedback [33] and usability testing sessions with SMART Recovery participants and facilitators, (3) clinical and research expertise from the members of the expert advisory and steering committees, and (4) technological and creative expertise of the development team employed to work on this study (GHO, Sydney) [34].

The functionality of Smart Track was initially tested with 3 members of the research team. Several bugs were identified and fixed before the amended beta version was released to a convenience sample (n=40) for further testing. This convenience sample of beta testers included members of the expert advisory committee, steering committee, SMART Recovery board members, and SMART Recovery facilitators. Further refinements were made in line with the feedback received (bug fixes, minor amendments to functionality, and content).

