#### Implementation Strategies

The app contains an in-built *walk through* to orient new users to the features of the app. We also intend to develop a brief tutorial to assist participants with app download and set up. Consistent with the recommendations for improving ROM uptake [9], SMART Recovery facilitators at each study site will assume the role of *local champions* of Smart Track. The research team will work with the facilitators to orient them to the app so that they are confident in responding to the participants’ questions about ROM completion and troubleshooting any difficulties that may arise. Participants and facilitators may also contact the research team directly for support. SMART Recovery facilitators will also prompt, encourage, and support study participants to regularly complete the ROM questions before and/or attending a SMART Recovery group.

In-app push notifications will also be used to prompt participants to complete the ROM items. In-app notifications (red marker) will also be used to highlight section(s) that require participants’ attention (eg, outstanding 7-day plan).

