#### Method of Dealing With Missing Data

Descriptive analyses will use all available data. Inferential analyses (eg, linear regression and growth curve modeling) will use multiple imputation (with chained regression equations) as the primary method of dealing with missing data. The number of imputed data sets will depend on the fraction of missing data, but the stability of results will be assessed over a range of imputation numbers.

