#### Power

We aim to recruit participants from 13 sites that conduct a combined total of 25 groups per week. Assuming an average of 6 eligible participants per group per week and a target sample size of 100 participants, we anticipate recruitment to take between 4 and 6 weeks (for an estimated recruitment rate between 11% and 17%). A sample of this size will enable the estimation of the recruitment rate and 95% CI, with a margin of error of no more than 7%.

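### Linear regression is named for time to disengagement, which is right-censored for anyone still using the app at 2 months, and the multiple-imputation rule does not exclude those times

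*Protocol article*

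**What the plan says.** Under App Engagement and Usage Patterns, usage is defined "as indexed by frequency of ROM completion, number of missing items" and time to disengagement. One model is named for all three: "time to disengagement) and participant characteristics (demographic, clinical, and treatment variables) will be explored using linear regression". Graphs and latent trajectory analysis follow, but no time-to-event method is named.

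The observation window is fixed in Table 3 (Study Outcomes), where missing ROM data are counted "across the 2-month period of Smart Track usage". The overview of Smart Track says that "ROM items are intended for weekly completion" and that "there are no contingencies for discontinuing access to the Smart Track app".

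Under Method of Dealing With Missing Data: "Inferential analyses (eg, linear regression and growth curve modeling) will use multiple imputation", by chained equations, as the primary method. Censoring is not mentioned there. The Power section gives "a target sample size of 100 participants".

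**The concern.** A participant who is still using the app when observation stops has no disengagement time. All that is known is that it exceeds about 2 months. Linear regression needs a number for that person, and there are three ways to supply one:

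- set the time to 2 months;
- leave the person out;
- treat the time as missing and impute it.

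The article does not say which applies. The imputation rule, read literally, leaves the third open: a chained-equation model could learn only from people who disengaged within the window, so it would give early exit times to the most engaged participants.

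At stake is the Table 4 endpoint on which demographic, clinical and treatment factors go with completing or not completing the ROM items. The people with censored times are the ones who separate characteristics that sustain use from those that do not.

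**Working it through.** **Plan's own figure.** There is none for this analysis. The Power section concerns the recruitment rate only.

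**Inputs from the article.** The window is 2 months = 2 × 365.25/12/7 = 8.7 weeks. The target is N = 100.

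**Assumptions, because the article gives no values.** The share still engaged at 2 months is varied from 5% to 70%. A binary characteristic splits participants equally. Times are either normal (SD 4 weeks, true difference 2 weeks) or exponential (hazard ratio 0.6).

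**Worked case: exponential times, 30% censored.** Solve 0.5·exp(−8.7λ) + 0.5·exp(−0.6·8.7λ) = 0.30, which gives λ = 0.180 per week. Write S = exp(−rate × 8.7). Differences are taken before rounding.

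| | Reference | HR 0.6 group | Difference (weeks) |
|---|---|---|---|
| Still engaged, S | 0.209 | 0.391 | |
| True mean, 1/rate | 5.56 | 9.26 | 3.71 |
| Capped at 8.7: (1 − S)/rate | 4.40 | 5.64 | 1.25 |
| Disengagers only: 1/rate − 8.7·S/(1 − S) | 3.26 | 3.68 | 0.42 |

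Capping recovers 1.25/3.71 = 34% of the unrestricted difference. Leaving out ongoing users recovers 0.42/3.71 = 11%. Imputing ongoing users from a regression fitted to disengagers aims at the same 0.42, because that is the only relation the imputation model can see. Measured against the 2-month restricted mean difference instead, 0.42/1.25 = 34% is left.

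**Share of the unrestricted difference recovered by linear regression (simulated):**

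| Still engaged | Normal, capped | Normal, left out | Exponential, capped | Exponential, left out |
|---|---|---|---|---|
| 5% | 95% | 82% | 81% | 53% |
| 20% | 80% | 59% | 48% | 20% |
| 30% | 70% | 50% | 34% | 11% |
| 50% | 50% | 37% | 15% | 4% |
| 70% | 29% | 26% | 5% | 1% |

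**Power at N = 100, exponential times, HR 0.6 (400 simulated trials per row):**

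| Still engaged | Linear, capped | Linear, ongoing users left out | Cox |
|---|---|---|---|
| 5% | 0.71 | 0.48 | 0.73 |
| 20% | 0.62 | 0.18 | 0.66 |
| 30% | 0.53 | 0.13 | 0.55 |
| 50% | 0.37 | 0.09 | 0.42 |

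The simulation error on a power near 0.55 is √(0.55 × 0.45/400) = 0.025, so capped regression and Cox are not clearly separated at 30%. Leaving out ongoing users is far below both.

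**The case against.** **Capping is defensible.** If every participant has the same window and use is logged daily, regression on capped times estimates the difference in mean engaged time over 2 months. That is a valid quantity, and its power is close to that of Cox. A reader might infer from the 34% figure that capped regression loses two thirds of the effect. The documents do not support that, because the full difference of 3.71 weeks rests on extrapolating an assumed exponential curve beyond the window. What remains is that the plan does not say it will cap or that a restricted mean is intended.

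**The plan does not say it will impute ongoing users.** This is correct. A reader might infer that it will, but the article never classes them as missing. It also does not rule this out, and the imputation rule is worded to cover linear regressions in general.

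**Two further readings do not hold.**

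- A reader might infer that participants are to be analysed as independent, since "SMART Recovery facilitators will also prompt, encourage, and support study participants to regularly complete the ROM questions" and usage could therefore cluster by site or group. The article is silent on clustering, and a condensed article may leave that to the analysis plan. In simulation, type I error for participant-level covariates unrelated to site stayed at 0.048 to 0.052. Inflation (0.133 at an assumed intraclass correlation of 0.10) needs a covariate that varies by site.
- A reader might infer that linear regression distorts the error bars for the bounded completion counts. Simulated type I error for a U-shaped 0–8 count at N = 100 was 0.048.

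**The analysis is exploratory.** It serves a secondary objective of a single-arm pilot whose primary endpoints are descriptive. That limits the weight of the point but does not make the named model suit a censored time.

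**Conclusion.** The point holds for time to disengagement alone. The article names a model that cannot represent right-censored times, although its fixed window and continued access mean that anyone still engaged at 2 months has one. The consequence depends on an unstated choice. Capping costs little power but gives a restricted mean difference that is not declared. Dropping ongoing users, or imputing them from disengagers, removes most of the association: at 30% still engaged, 50% (normal times) to 11% (exponential times) is recovered, and power falls to 0.13 against 0.55 for Cox.

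The share still engaged, the time distributions and the hazard ratio are assumptions. The pull towards zero when ongoing users are left out appeared in every scenario run, and its size grows with the share censored. The correction is worth making, but the primary objectives do not depend on it.

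**What to change.** - Replace linear regression for time to disengagement with Cox or discrete-time (weekly) survival regression, with administrative censoring at 2 months. Alternatively, keep a mean difference and declare the 2-month restricted mean as the estimand, with ongoing users set to the end of the window.
- State in the missing-data section that censored disengagement times are not missing data and are not imputed.

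This needs only wording and standard software, with no new data or participants. The downside of the survival model is a hazard ratio, which is less familiar than a difference in weeks.

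Optional good practice, not a correction: a count or proportion model for completions and missing items, and cluster-robust standard errors by site or group.
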